### c) Analytical procedures including measures of precision such as confidence intervals

Not applicable.

### d) The significance level of the power of primary endpoint(s)

Statistical significance level will be set at 5%.

### e) Sample size calculation and justification

The primary endpoint of the clinical trial is the distance covered during the 6-minutes' walk test. The sample size was calculated based on a study comparing passive and quasi-passive prosthetic ankles which found an effect size Cohens'  $f = 0.318$  on distance covered during the 6-minutes' walk test [4]. A total of 40 participants with a lower limb amputation is required and will be allocated to one of the two prosthetic groups. These individuals will be stratified by age (2 strata:  $< 45$  years,  $\geq 45$  years, block size = 4) to control for age-related cognitive deterioration. A matched control-group of 20 able-bodied individuals will be included to enable comparison. The required number of 40 participants with amputation is based on a sample size calculation for an analysis of variance using G\*Power (version 3.1.9.4) envisaging 10% drop-out. Values used for this calculation were medium expected effect size  $f = 0.318$ , power = 0.80,  $\alpha = 0.05$ , the number of groups = 3 and the number of measurements set at 2 with a correlation between measurements of 0.75.

- f) The rationale for the number of procedures to be performed by a single user as part of the learning curves

A baseline experiment with a conventional prosthetic ankle used in rehabilitation is required to observe any similarities or differences in outcomes with the LUNARIS®. Moreover, a baseline experiment with able-bodied subjects is required to observe any similarities or differences in outcomes with the LUNARIS®. Therefore, each lower-limb amputee is asked to schedule four appointments and each able-bodied subject is asked to schedule two appointments to run through the whole experiment.

- g) Pass / Fail criteria to be applied to the results of the clinical investigation

Not applicable.

- h) The provision for an interim analysis

Not applicable.

- i) Management of bias

All appointments for the MRI will take place at UZ Brussel to avoid any bias due to a different MRI scanner. All appointments for functional performance testing will take place at Axiles Bionics to avoid any bias due to different slopes or staircases between subjects and between sessions.

- j) Management of potential confounding factors

Not applicable.

- k) Description of procedures for multiplicity control and adjustment of error probabilities

The principal investigator and co-investigators will analyse the data independently to identify any error probabilities.

- l) The specification of subgroups for analysis

Not applicable.

- m) Management, justification and documentation of missing data

Drop-outs and unused data will not be included in the analyses. We ensure that any unused or spurious data (including drop-outs) will be fully recorded by the investigators, manufacturer or other parties, and immediately notified to sponsor to all competent authorities (including FAMHP) by using the European form in a timely manner.

- n) Exploratory analysis and sensitivity analysis

Not applicable.

o) Procedures for reporting any deviation(s) from the original statistical analysis plan

We ensure that any deviation will be fully recorded by the investigators, manufacturer or other parties, and immediately notified to sponsor to all competent authorities (including FAMHP) by using the European form in a timely manner.

p) A strategy for handling the potential imbalance of the number of subjects across investigation sites

Not applicable since each subject of this clinical investigation will perform the different experiments in the two same investigation sites.

q) A strategy for pooling data

All data will be entered in excel and physical copies will be scanned as a pdf file. During the investigation, data will be saved on the VUB share point, which has a built-in back-up. After the investigation, data will be anonymized where possible and stored in the VUB university archive.

As personal and sensitive data of human participants will be collected, pseudonymisation of the data will take place as soon as possible upon data acquisition. The file which establishes the link between the pseudonymised identities and the identification of the participant, will be password- protected.

All raw data will be stored in the online system of the Ethical Committee of the UZ Brussel (i.e., Redcap). Raw and cleaned data will also be stored and encrypted on the research's group network attached storage (NAS) under supervision of [name] [name]. The NAS is system-encrypted, back-upped, has up-to-date antivirus and is only accessible by authorised personnel. Passwords will be required to access the NAS, in compliance with the GDPR regulations. All manual files and written data will be stored in locked filing cabinets. All anonymized data will be stored for up to 10 years as recommended by the VUB.

Option to access the database will require a data use agreement. The stored data will remain unchanged and be identified by the researcher ORCID and article DOI. Transfer of data will only be done if essential.

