### c) Scientific justification and clinical relevance for effect sizes

The primary endpoint of the clinical trial is the distance covered during the 6-minutes' walk test. The sample size was calculated based on a study comparing passive and quasi-passive prosthetic ankles which found an effect size Cohens'  $f = 0.318$  on distance covered during the 6-minutes' walk test [4]. A total of 40 participants with a lower limb amputation is required and will be allocated to one of the two prosthetic groups. These individuals will be stratified by age (2 strata:  $< 45$  years,  $\geq 45$  years, block size = 4) to control for age-related cognitive deterioration. A matched control-group of 20 able-bodied individuals will be included to enable comparison. The required number of 40 participants with amputation is based on a sample size calculation for an analysis of variance using G\*Power (version 3.1.9.4) envisaging 10% drop-out. Values used for this calculation were medium expected effect size  $f = 0.318$ , power = 0.80,  $\alpha = 0.05$ , the number of groups = 3 and the number of measurements set at 2 with a correlation between measurements of 0.75.

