## 6. Design of the clinical investigation

### 6.1. General

#### a) Description of the design type of clinical investigation to be performed

This cohort study includes three groups.

- 20 lower-limb amputees who are going to do their rehabilitation and perform daily activities with a new articulated ankle foot prosthesis: the LUNARIS®.
- 20 lower-limb amputees who are going to do their rehabilitation and perform daily activities with a conventional prosthetic ankle: the SACH® followed by the most suited prosthesis for them.
- 20 able-bodied subjects which will be used as a control group.

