#### d) Procedures to maintain and protect subject privacy

As personal information is branded by the EU as sensitive, data will be anonymized as soon as possible. Participants will receive a code corresponding to their inclusion order, and the file that relates these codes to their personal information will be encrypted. During the course of the study, data will only be stored with personal access, on a personal cloud server. After the study completion, all data will be shared with the research lab through a network attached storage.

As personal and sensitive data of human participants will be collected, pseudonymisation of the data will take place as soon as possible upon data acquisition. The file which establishes the link between the pseudonymised identities and the identification of the participant, will be password-protected.

The data protection officer of the VUB ([contact]) will be notified of our study. Data in the present study will be managed confidentially, conforming to the Algemene Verordening Gegevensbescherming (GDPR) of 27 April 2016.

Participating in this study means that the participant agrees that the investigators gather data of the participant that will be used to conduct the investigation and eventually will result in the publications in scientific journals and presentations at conferences. The participant will always have the right to ask the investigators which data he/she has gathered on them and for what this data is used in light of the investigation. The participant retains the right to look into this data and to ask for corrections on the occasion this data would contain errors. The participant also retains the right to stop his/her participation in the study at any moment.

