#### Statement D

The submitters of the present protocol proposal declare no financial or other conflicts of interest.

Trial results will be communicated to the general public through the publication of disseminated manuscripts published in scientific journals, and through conference presentations/posters. Authorship of these papers and presentations will only be granted to researchers that performed a substantial contribution to the scientific article. Public access will be granted to the entire protocol through the Clinicaltrials.gov registry. The statistical code and dataset will only be shared upon reasonable request, and the responsible data managers reserve the right to refuse such requests.

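### The published fixed block size of 4, with no concealment described, lets about 30–33% of device assignments be deduced in advance if the blocks are random, and possibly all of them if they are not

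*Protocol*

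**What the plan says.** The same paragraph appears in Sections 5 c) and 7 e). It states that "A total of 40 participants with a lower limb amputation is required and will be allocated to one of the two prosthetic groups", and then: "These individuals will be stratified by age (2 strata: $< 45$ years, $\geq 45$ years, block size = 4". The stated purpose is to control for cognitive decline with age. No other allocation rule appears in the protocol.

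Other sections bear on it:

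- **Section 6.1 a)** calls the study a cohort study and sets 20 amputees per device: "20 lower-limb amputees who are going to do their rehabilitation and perform daily activities with a new articulated ankle foot prosthesis" and "20 lower-limb amputees who are going to do their rehabilitation and perform daily activities with a conventional prosthetic ankle".
- **Section 6.3 e)**, under the heading on the point of randomisation, says that the study is not randomised.
- **Section 6.1 d)** places allocation after the week-0 MRI. The first functional tests, including the 6-minute walk, come at week 12.
- **Sections 6.1 b) and 7 i)** limit bias control to one scanner and one test location. Neither concealment nor blinding is described.
- **Section 17, Statement D**: "Public access will be granted to the entire protocol through the Clinicaltrials.gov registry".

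**The concern.** A block rule with one known size can be predicted even when the order inside each block is random. Once one device has used up its share of a block, the remaining assignments are forced. Here the size is printed in a document that will be public, the strata are two age bands that are easily determined, and an articulated foot can be told from a SACH foot by sight, so past assignments are not hidden.

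Someone who knows which device comes next can decide whom to approach, or when to book the week-0 scan, and so place stronger or weaker walkers in a given arm. The primary endpoint is walking distance, and the first walking test comes after 12 weeks on the allocated foot. That test cannot serve as a pre-allocation measure of walking ability.

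**Working it through.** **Inputs.** Block size 4, two age strata and 40 amputees come from Section 7 e). The 1:1 ratio is inferred from the 20 and 20 in Section 6.1 a). Stratum sizes are not given. The protocol states no predictability figure to reproduce. Steps 1 to 5 assume randomly permuted 2:2 blocks, which the protocol does not state.

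**1. Deducible assignments, complete blocks.** There are six equally likely orderings. In two of them (AABB, BBAA) the third and fourth assignments are forced. In the other four only the fourth is forced.

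(2 × 2 + 4 × 1) / 6 = 8/6 = 1.333 per block of 4 = 33.3%

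Ten complete blocks give 10 × 1.333 = 13.3 of 40 (simulated 95% range 11 to 16).

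**2. Incomplete last blocks.** A block cut off after 1, 2 or 3 patients contains on average 0, 0 or 1/3 forced assignments. The strata sum to 40, so the leftovers are (0, 0), (1, 3) or (2, 2):

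- (0, 0): 13.3 of 40 = 33.3%
- (1, 3): 9 × 1.333 + 0 + 0.333 = 12.3 of 40 = 30.8%
- (2, 2): 9 × 1.333 + 0 + 0 = 12.0 of 40 = 30.0%

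**3. Best guess.** Guessing the device that is behind in the block is right with probability 1/2, 2/3, 2/3 and 1 at the four positions. The sum is 2.833 of 4 = 70.8%. With leftovers (1, 3) or (2, 2) it is 27.83 of 40 = 69.6%.

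**4. Spurious arm difference.** Assume that the recruiter shifts expected walking ability by δ in the direction of the predicted device, and that the device has no effect.

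- Acting only on forced slots: arm means are +δ/3 and −δ/3, a difference of 2δ/3. This is 0.17 SD for δ = 0.25 and 0.33 SD for δ = 0.50.
- Acting on every best guess: the difference is 2δ(2 × 0.708 − 1) = 0.833δ. This is 0.21 SD and 0.42 SD.

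**5. False-positive rate.** Simulation: 5,000 trials, two strata of 20, two-sided t-test at 5%, no device effect. Ranges show repeat runs.

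| Scheme and behaviour | δ = 0.25 SD | δ = 0.50 SD |
|---|---|---|
| Fixed 4, forced slots only | 0.17 SD; 7.7% | 0.34 SD; 16.5–16.7% |
| Fixed 4, every best guess | 0.21 SD; 9.1–9.7% | 0.42 SD; 22.1–22.2% |
| Varying 4/6/8, guess from running imbalance | 0.17 SD; 7.9% | 0.34–0.35 SD; 15.5–16.8% |

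The simulated differences agree with step 4. With strata of 13 and 27, forced slots only and δ = 0.50 SD, the result is 0.31 SD and 15.2%.

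**6. If Section 6.3 e) is taken literally.** With a non-random assignment rule steps 1 to 5 do not apply, and up to 100% of assignments could be known in advance.

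**The case against.** The strongest objection is that the protocol never says that the blocks are random. It says the opposite in Section 6.3 e) and calls the study a cohort study. A reader might infer from the block size that one third of assignments are certain to be known in advance. That does not follow: the figure is conditional on random 2:2 blocks, falls to 30% with incomplete blocks, and requires knowledge of every preceding assignment in the stratum. This part of the objection stands. It does not rescue the plan, because a non-random rule may be more predictable still.

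Three further inferences also go beyond the text:

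- **That the investigators who test the patients also allocate them and see the whole sequence.** No section says who allocates. Section 6.3 d) recruits through several centres, and a recruiter at one of them may see only part of a shared sequence. Testers meet the patients at week 12, well after allocation.
- **That the participant code reveals the position in a block.** Section 8 d) says "Participants will receive a code corresponding to their inclusion order". It does not tie the code to an age stratum or restrict it to amputees, and the linking file is encrypted. The code alone does not give the position.
- **That steering could never be detected or adjusted for.** Section 7 b) lists age, time since amputation and prosthesis history among its covariates, and Section 6.3 a) restricts entry to K3–K4. These allow a partial check. They do not replace a measure of walking ability before allocation.

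It is also fair to say that the shift of 0.25 to 0.50 SD is assumed, that it presumes deliberate steering in a scarce population, and that varying the block size alone recovers little. All of this stands and shapes the fix. Details of list generation may properly be kept outside a protocol, but here the protocol itself fixes and publishes the block size.

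**Conclusion.** The concern holds in conditional form. If the blocks are randomly permuted 2:2, 12.0 to 13.3 of the 40 device assignments (30% to 33%) can be deduced beforehand by anyone who knows the earlier ones in the stratum, and a best guess succeeds about 71% of the time. If allocation is not random, predictability may be complete. On neither reading does the protocol describe anything that hides the next assignment.

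The predictability figures rest on the 1:1 ratio and random order. The bias of about 0.17 to 0.42 SD and the false-positive rate of about 8% to 22% rest in addition on the assumed steering shift. They show what is possible and do not forecast what will happen. The protocol gives no standard deviation for walking distance, so the bias is left in SD units.

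**What to change.** Before the first patient is enrolled:

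1. Reconcile Sections 5 c) and 7 e) with Sections 6.1 a) and 6.3 e). If blocked allocation is kept, state that it is random and correct the other two sections. If the study is to stay non-randomised, remove the block wording and state how the device is assigned.
2. If blocks are kept, delete the block size from Sections 5 c) and 7 e). Use randomly varying sizes (for example 4, 6 and 8) within the two existing age strata, recorded only in a restricted file.
3. Have the list generated and held centrally by someone not involved in recruitment or testing, for example in the REDCap system that Section 8 f) already names. Release each assignment only after consent and the week-0 MRI are logged.

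The third step gives the main protection. Under the 0.50 SD assumption, varying the block size alone lowers the bias only from about 0.42 to 0.35 SD. Concealment until the patient is irrevocably enrolled removes the opportunity to choose patients for a known slot.

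The cost is a few sentences of protocol text and one list set up in an existing system. Arm sizes may differ from 20/20 by a few patients if the last block in a stratum is incomplete.

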## 2. Identification and description of the investigational device

### a) Summary description of the investigational device

The LUNARIS® is an external ankle-foot prosthetic component with an articulated ankle-joint and internal sensors. It is intended for the replacement of the ankle-foot to compensate for a lower-limb deficiency. It is to be used exclusively for the non-invasive, exo-prosthetic fitting of the lower limb prosthesis, as prescribed by a healthcare professional. It is designed for single-patient use and supports low to moderate impact use. It is developed to fulfil basic daily activities such as standing, walking, stair ascending and descending, slope ascending and descending, sitting, in indoor and outdoor environments.

The LUNARIS® is delivered with its smart charger, the IO® CHARGER. This smart charger is an accessory intended to charge the LUNARIS® and to transfer the data gathered during the day to the Axiles Bionics secured cloud based service for the purpose of predictive maintenance.

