#### d) Methods and timing for assessing, recording and analysing variables

##### Population & sample size:

Adults aged 25-65 with a transtibial amputation will be recruited through contacting rehabilitation centres, and orthopaedic departments of hospitals within the network of BruBotics ([BruBotics.eu](https://BruBotics.eu)) and Axiles Bionics ([Axiles Bionics | Next Generation Bionics](https://AxilesBionics.com)). Adults with a Medicare Functional Classification level lower than K3, metal implants, bilateral amputation, additional upper-limb amputation or diabetes will be excluded as well as participants with neurological disorders or with excessive stump pains and wounds. All participants will be asked to provide their written consent after being written and verbally informed regarding the study protocol. The study will be executed in compliance with the Declaration of Helsinki [10] and Ethical approval will be sought from the medical ethics commission of VUB and UZ Brussel.

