## 6.3. Subjects

### a) Inclusion criteria for subject selection

- Age: 25 - 65 years
- Gender: men and women
- Level of amputation: unilateral transtibial
- Medicare Functional Classification Level: K3-K4

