### e) Point of randomization

Non-randomized.

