### d) The methods for addressing these factors in the clinical investigation

Specific inclusion and exclusion criteria are applied before enrolment to counteract as possible factors that can compromise the outcome.

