### b) Descriptive statistics of baseline data

#### *Functional performance testing*

A mixed model will be constructed enabling within and between group (i.e., type of prosthesis) comparison of balance performance and accounting for baseline covariates. If residuals are not normally distributed, required adaptations to the data or model will be performed. To correct for multiple comparisons, suited corrections will be applied. The factors age, time since amputation, side of amputation, level of amputation, time using prosthesis, previously used prosthesis will be accounted for. Statistical significance level will be set at 5%.

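### K3 and K4 users are both eligible in a non-randomized comparison, but the factors named for the walking model omit K-level, the only functional measure required before allocation

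*Protocol*

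**What the plan says.** **Eligibility.** Protocol 6.3 a) admits "Medicare Functional Classification Level: K3-K4" and restricts amputation level to unilateral transtibial. Section 6.1 d) excludes "Adults with a Medicare Functional Classification level lower than K3". K-level must therefore be known for every participant with an amputation before entry.

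**Group formation.** Section 7 e) (repeated in 5 c) says "These individuals will be stratified by age (2 strata", split at 45 years, with "block size = 4) to control for age-related cognitive deterioration". No other balancing factor is named. Section 6.3 e) describes the study as "Non-randomized".

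**Timing.** Under 6.1 d) and 6.4 a), week 0 has an MRI scan only. Allocation follows. Functional tests are first done at week 12 and repeated at week 24.

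**Analysis.** For functional performance, 7 b) plans a mixed model with within- and between-group comparison that accounts for baseline covariates, and then says: "The factors age, time since amputation, side of amputation, level of amputation, time using prosthesis, previously used prosthesis will be accounted for". K-level is not among these factors, nor among those listed for the brain analysis.

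**Confounding.** Section 7 j) is marked not applicable. Section 6.4 d) relies on eligibility: "Specific inclusion and exclusion criteria are applied before enrolment to counteract as possible factors that can compromise the outcome".

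**Endpoint.** The primary endpoint is 6-minute walk distance, with a relevance threshold of 35 m (6.1 e). H1 in 5 d) compares this distance between users of the two types of prosthesis.

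**The concern.** The comparison is non-randomized with 20 patients per prosthesis group, so nothing in the design makes the groups alike in walking ability at the start. Adjustment has to do that work, and it can only use what is measured before allocation.

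The protocol requires one functional grading at that point, the K-level, and then uses it only as an entry threshold. The criteria cited in 6.4 d) cut off the levels below K3 but leave two levels in, so they do not settle this factor. The single stratum, age, was chosen for a cognitive reason and not for walking capacity.

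At stake is the reading of H1. A difference in distance at week 12 or week 24 could partly reflect a different K3/K4 mix, and the factors named for the model offer no way to separate this from the effect of the foot.

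**Working it through.** The plan calculates nothing on this point, so there is no stated figure to reproduce. The sample size of 40 enters only as 20 per prosthesis group.

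**Step 1: what is measured before allocation.**

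| Time | Assessment | Before allocation? |
|---|---|---|
| Entry | K-level, to apply 6.3 a) | yes |
| Week 0 | MRI | yes |
| Week 12 | First functional tests, including the 6-minute walk | no, after 12 weeks on the allocated foot |
| Week 24 | MRI and functional tests | no |

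K-level is the only functional measure in the rows marked yes.

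**Step 2: can the named factors stand in for it?**

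- Amputation level: constant under 6.3 a), so it adjusts for nothing in the comparison of the two prosthesis groups.
- Time using a prosthesis and previously used prosthesis: participants join at the start of rehabilitation, when they learn to walk with a prosthesis (6.1 d). These factors may vary little at that point. This is an inference; the protocol gives no distribution.
- Age, time since amputation and side of amputation: these vary, but none grades function.

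**Step 3: size of the possible shift.**

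Inputs:
- Group size: 20 per prosthesis group (6.1 a).
- Relevance threshold: 35 m (6.1 e).
- D, the K4-K3 gap in distance: not in the protocol; assumed 60-120 m, with K4 users walking further.
- Δ, the difference in K4 share between groups: not in the protocol; illustrated at 4/20 = 0.20.

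Formula: shift in the group difference = Δ × D.

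- D = 60 m: 0.20 × 60 = 12 m, and 12/35 = 34% of the threshold.
- D = 120 m: 0.20 × 120 = 24 m, and 24/35 = 69% of the threshold.

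The imbalance that would produce 35 m on its own is 35/D:
- D = 60 m: 35/60 = 0.58, or about 12 of 20 patients.
- D = 120 m: 35/120 = 0.29, or about 6 of 20 patients.

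**Step 4: is a 20-point gap unusual?** As a reference only, suppose allocation were random at 20 v 20. With each patient having a 50% chance of being K4, the probability of a gap of at least 20 points is 0.27. With exactly 20 of the 40 being K4, it is 0.34. Under non-random allocation these probabilities do not apply, and a gap may be larger and systematic.

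**Step 5: does analysing change remove the problem?** Write the group difference at week 12 as τ12 + ΔD and at week 24 as τ24 + ΔD, where τ is the device effect. The change contrast is (τ24 + ΔD) − (τ12 + ΔD) = τ24 − τ12. A constant K-level offset cancels. So does whatever device effect had already appeared by week 12, because that measurement is post-exposure.

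**The case against.** Several points on the other side stand.

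- **The list may not be exhaustive.** Section 7 b) refers to baseline covariates in general before naming factors, and an analysis plan not shown here could add K-level. But the protocol itself chose which factors to name, included one that is constant, and marked confounding as not applicable. The general phrase does not commit to K-level.
- **A change contrast cancels a constant offset.** This is correct (step 5), so it would be wrong to say that the planned model cannot deal with K-level. The contrast answers a narrower question than H1.
- **The metre figures are assumptions.** The protocol gives neither a K4-K3 gap nor a K4 share. At the illustrated imbalance the shift stays below 35 m. Since participants enter at the start of rehabilitation, K-level may be an expected rather than an observed level. Nothing in the protocol supports calling it the strongest predictor of distance.
- **Recording is not stated.** That K-level must be established follows from eligibility; that it is kept as a variable does not.
- **Age is not irrelevant to the functional tests.** The dual-task test scores subtractions, and age is also a factor in the walking model. The criticism is only that the stratum leaves functional level open.
- **Chance imbalance under random allocation is sampling variation, not bias.** Confounding in the systematic sense depends on the non-random allocation.

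A reader might also infer from the device description ("It is designed for single-patient use and supports low to moderate impact use") that the most active patients will be steered to the other foot, or that the admitted K-range conflicts with the device's intended use. The documents do not support either. No passage says that a prosthetist chooses the group, none maps impact level to K-level, and the instructions for use are not at hand.

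**Conclusion.** The point holds as a conditional risk. The protocol admits two functional levels, does not randomize, performs no walking test before allocation, and names model factors that include a constant but omit the one functional grading it must already have. If the groups differ in K4 share and K4 users walk further, the between-group comparison of 6-minute distance is confounded.

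The size is unknown from the documents. Under the assumed 60-120 m gap and a 20-point imbalance, the shift is 12-24 m, roughly one to two thirds of the 35 m threshold. It would be zero with balanced groups or no gap, and a constant offset would drop out of a week 12 to 24 change contrast.

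It would go too far to conclude that the primary comparison is biased as it stands, since no imbalance is shown. Nor would handling K-level cure the non-random allocation, because other selection factors would remain open.

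**What to change.** In 7 b), state that K-level (K3 or K4) is recorded before allocation, and add it as a covariate in the walking model for the comparison of the two prosthesis groups. It can replace amputation level, which is constant under 6.3 a). Amend 7 j) so that it no longer marks confounding as not applicable and refers to this adjustment.

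Balancing group formation on K-level as well is optional. Crossing two age strata with two K-levels gives four cells, on average 40/4 = 10 patients each, so blocks of four would often be left incomplete. The covariate is the simpler route.

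While these sections are open, the stratified blocks in 7 e) and the non-randomized statement in 6.3 e) should be reconciled, since the reader cannot tell from them how groups are formed.

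The cost is protocol wording and one model term, or no net term if amputation level is dropped. No new assessment is needed, because K-level is already required for eligibility. The recording rule should be in place before the first participant is allocated.
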